#### Combined Endo‐Epicardial Approach

2.3.3

Regarding antithrombotic management: (i) for patients on DOACs, the last dose should be taken at least 3 days before the procedure (apixaban and rivaroxaban) or 4 days before (dabigatran); (ii) for patients on VKAs, therapy will be discontinued 5 days before the procedure, which can be performed if the INR is < 1.5 on the day before the procedure; (iii) for patients on antiplatelet agents, aspirin will be continued alone and any other antiplatelet agent will be halted at least 5 days before the procedure.

The defibrillator will be deactivated at the beginning of the procedure. A quadripolar catheter will be placed inside the right ventricle to pace the ventricle during the procedure if needed for VT induction/overdrive and to perform programmed ventricular stimulation at the end of the procedure.

The first step of the procedure will aim at obtaining pericardial access, which will be performed using a Tuohy needle. To minimize the risk of complications, an anterior approach will be preferred, using fluoroscopy in the lateral projection to avoid diaphragmatic puncture, and a long guidewire will be placed before advancing the sheath to confirm intrapericardial placement. Other specific techniques may be used according to the operator's preference (e.g., micropuncture, CO2 insufflation). A deflectable sheath will then be introduced into the pericardium, and a high‐density mapping of the epicardium in sinus rhythm/pacing will be performed to identify low‐voltage areas and search for the presence of late potentials, abnormal ventricular electrograms, and deceleration zones. The left phrenic nerve will be located by high‐output stimulation (10 mA), and its position annotated on the map.

After completing the epicardial map, before mapping the left ventricular endocardium, and in the absence of pericardial bleeding related to the puncture, unfractionated heparin will be administered (100–120 IU/kg) and then regularly during the procedure to maintain an ACT of approximately 300 s.

Endocardial access to the left ventricle will be obtained via a retrograde aortic approach (through femoral arterial puncture) and/or a transseptal approach (through femoral venous puncture) according to the center's usual practice and the presumed location of the VT. A high‐density map during sinus rhythm or pacing will be created to identify low‐voltage areas and the presence of late potentials, abnormal ventricular electrograms, and deceleration zones.

Once the endocardial and epicardial surfaces will have been mapped, VT induction will be attempted if desired to perform an activation map. A complete substrate ablation strategy will be employed, complemented by specific strategies for the ablation of induced VTs (pace mapping and entrainment mapping). Radiofrequency energy will be delivered using irrigated tip catheters at 30–50 W, preferably with isotonic saline, for a maximum duration of 60 s: (i) For the endocardial substrate and VTs, a complete substrate ablation strategy will be employed, complemented by specific strategies for the ablation of induced VTs (pace mapping and entrainment mapping). (ii) For the epicardial substrate and VTs, after identifying the areas requiring ablation (substrate ablation strategy, complemented by specific strategies for the ablation of induced VTs using pace‐mapping and entrainment mapping), their positions relative to the phrenic nerve (previously located by stimulation during mapping) and coronary arteries (using fused imaging from a CT scan or intra‐procedural coronary angiography) will be evaluated to determine whether ablation is achievable.

At the end of the procedure, programmed ventricular stimulation will be performed to assess the inducibility of the clinical or other nonclinical VTs, thereby determining the acute success or failure of the procedure. A standardized protocol will be followed, with stimulation at two different cycle lengths (600 and 400 ms) and up to three extrastimuli decrementing to 200 ms (or the ventricular refractory period). For non‐inducible patients, the procedure will be concluded. For patients with inducible VTs, ablation will continue, specifically targeting the induced VTs.

Acute procedural success will be defined by both the absence of VT inducibility on programmed ventricular stimulation and complete substrate modification, including the elimination of arrhythmogenic sites such as local abnormal ventricular activities. To confirm the efficacy of substrate modification, systematic postablation remapping will be performed.

A pericardial drain may be left in place overnight, and intrapericardial injection steroid injection performed at the discretion of the operator.

The defibrillator will be reactivated at the end of the procedure.

#### Before Hospital Discharge

2.3.4

Transthoracic echocardiography will be performed on the day after the procedure to ensure the absence of pericardial complications. ICDs will be programmed as recommended by guidelines [22], as follows: (i) VF Zone: ≥ 220 bpm, with high‐energy shocks; program 1 burst of ATP before or during charging; long detection intervals (at least 20) should be programmed; (ii) VT Zone: 10–20 bpm slower than the clinical VT rate if known, potentially separated into VT1 and VT2 zones; at least 3 bursts of ATP before delivering shocks in the VT1 zone, and at least 1 burst in the VT2 zone, followed by high‐energy shocks; long detection intervals should be programmed; (iii) Monitor Zone: recommended at 150–160 bpm (if the VT zone extends below this rate, a Monitor Zone is not necessary); (iv) Base Rate: set at 30–40 bpm unless pacing is indicated; (v) SVT discriminators should be programmed ON. Patients will be discharged 24–48 h after the procedure, provided that there are no complications. Upon discharge, a remote‐monitoring report will be scheduled on a monthly basis.

Management of antiarrhythmic drug therapy postablation will be left to the discretion of the treating physician. However, the study protocol recommends discontinuation of AADs whenever feasible. The use of AADs, including initiation, continuation, or discontinuation, will be systematically recorded during follow‐up to assess their potential impact on study outcomes.

### Follow‐Up Visit

2.4

The patient will receive a telephone call at 6 and 18 months, and will be seen in a consultation at 1 and 2 years following the procedure. This will allow the medical team to inquire about any hospitalizations and the use of antiarrhythmic medications. Remote monitoring will be used to retrieve any recorded arrhythmic event. In the event of hospitalization or consultation, the center or healthcare professional who manages the patient will be contacted to obtain hospitalization reports and check for the occurrence of ventricular arrhythmia.

After 2 years of follow‐up, patients included in the study with a successful procedure and no recurrence will be followed up remotely until (i) arrhythmia recurrence or at the latest, or (ii) the date of the last visit of the last patient included.

Of note, if a new ablation is required during follow‐up due to arrhythmia recurrence, the choice of approach (endocardial only or combined endo‐epicardial approach) will be left to the discretion of the medical team in charge of the patient.

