At the end of the procedure, programmed ventricular stimulation will be used to assess the inducibility of clinical or other nonclinical VTs, thereby determining the acute success or failure of the procedure. A standardized protocol will be followed, with stimulation at two different cycle lengths (600 and 400 ms) and up to three extrastimuli decrementing to 200 ms (or the ventricular refractory period). For non‐inducible patients, the procedure will be concluded. For patients with inducible VTs, ablation will continue, specifically targeting the induced VTs.

Acute procedural success will be defined by both the absence of VT inducibility on programmed ventricular stimulation and complete substrate modification, including the elimination of arrhythmogenic sites such as local abnormal ventricular activities. To confirm the efficacy of substrate modification, systematic postablation remapping will be performed.

Crossover to an epicardial approach will not permitted during the index procedure. If VT remains inducible despite endocardial ablation, patients will continue follow‐up as per protocol. Any recurrence of VT will be considered as meeting the primary outcome, and subsequent management, including potential epicardial access, will be left to the discretion of the treating physician outside of the initial study intervention. Patients will be analyzed on an intention‐to‐treat basis.

The defibrillator will be reactivated at the end of the procedure.

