#### Primary Outcome

2.6.1

The primary endpoint is survival without ventricular arrhythmia recurrence, defined as the interval between the date of ablation and the date of the first recurrence of ventricular arrhythmia. Ventricular arrhythmia recurrence will be defined as the occurrence of an appropriate therapy delivered by the ICD or the occurrence of sustained VT/VF lasting more than 30 s requiring hospitalization. The occurrence and date of the event will be obtained from ICD interrogation. Patients without recurrence will be censored on the date of the last ICD interrogation.

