#### Secondary Outcome

2.6.2

The secondary outcomes are: (i) the number of ventricular arrhythmias requiring ICD treatment or hospitalization; (ii) the percentage of patients with ventricular arrhythmia recurrence at 2 years; (iii) the percentage of patients experiencing an electrical storm at 2 years, defined as the occurrence of at least three appropriate therapies (ATP or shocks) delivered by the ICD within 24 h; (iv) the rate of serious complications related to the procedure at 1 month; (v) procedure duration (from puncture to catheter removal, in minutes) and radiofrequency duration (in minutes); (vi) the number of patients hospitalized for cardiovascular reasons (e.g., heart failure, arrhythmias) at 2 years; (vii) the number of patients requiring a repeat ablation; (viii) the mortality rate at 2 years; (ix) the number of patients with non‐inducibility at the end of the procedure; (x) the percentage of patients who experienced inappropriate therapy at 2 years; (x) the duration of hospitalization postablation (days from ablation to hospital discharge) to assess post‐procedural recovery.

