#### Sample Size Estimation

2.7.1

In two meta‐analyses investigating ICM patients outcomes after endo‐epicardial ablation, the risk of ventricular arrhythmia recurrence at 2 years was 50% in the ‘endocardial‐only’ group and 26% in the ‘endo‐epicardial’ group (HR = 0.43) [20, 21]. To demonstrate this difference, it is necessary to observe 59 events to ensure 90% power with a two‐sided α risk of 5%. To observe a minimum of 59 events required for analysis, we planned to evaluate 150 patients followed for a period of at least 2 years. After the 2‐year follow‐up, patients will no longer be monitored as part of the study, but the ICDs will be remotely interrogated via telemonitoring for patients with no recurrence until (i) arrhythmia recurrence or at the latest (ii) the date of the last visit of the last patient included.

Of note, the sample size estimation is based on treatment effect derived from a prior meta‐analysis of observational studies. However, we acknowledge that the endocardial ablation strategies varied significantly across the included studies, ranging from targeted ablation of clinical/induced VT to complete scar homogenization. This heterogeneity may have influenced the estimated benefit of a combined endo‐epicardial approach and represents a limitation of the current power calculation.

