Consequently, few studies have attempted to evaluate whether a combined endo‐epicardial ablation could result in better procedural outcomes after RF ablation. Some retrospective observational studies have analyzed the recurrence of VT in patients with ICM based on whether the ablation was performed via the endocardial or endo‐epicardial approach, with conflicting results [14, 15, 16, 17, 18, 19]. A recent meta‐analysis of six studies suggests an advantage of the endo‐epicardial approach over the endocardial approach (Relative risk reduction (RRR) = 0.43 [95% CI: 0.28–0.67]). No differences in terms of acute procedural success nor all‐cause mortality were observed, while a nonsignificant trend towards a higher risk of complication was noted (RRR = 1.88 [95% CI: 0.19–18.76]). [20] Bisceglia et al recently reported a low 3.6% risk of complications when epicardial ablation is performed in experienced centers [11]. More recently, Mohanty and al observed in a study of 361 patients with ICM VT that those receiving combined endo‐epicardial ablation had significantly lower 5‐year VT recurrence rates (45.6%) than those with only endocardial ablation (89.1%; *p* = 0.01) [26]. After adjustment, epicardial ablation significantly reduced VT recurrence risk (Hazard Ratio = 0.48; 95% CI = 0.27–0.86; *p* = 0.02). Although many studies have reported the safety and efficacy of a combined strategy in ICM patients, the level of evidence remains low, mainly based on retrospective observations with small patient populations, and no controlled, randomized study has confirmed this hypothesis. Notably, only one clinical trial (NCT02358746) has been registered since 2015 to evaluate this question, but was stopped due to inclusion issues.

The aim of the proposed multicentre, prospective, randomized trial is then to determine whether a first‐line combined endo‐epicardial ablation improves long‐term arrhythmia‐free survival in ICM patients compared to an endocardial‐only approach.

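### Sections 2.4 and 2.7.1 give incompatible rules for follow-up after 24 months, and the section 2.4 rule would tie censoring in the primary analysis to a post-randomisation result

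*Protocol article*

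**What the plan says.** All references are to the protocol article.

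- **Section 2.4 (Follow-Up Visit):** after two years, "patients included in the study with a successful procedure and no recurrence will be followed up remotely until" recurrence or, at the latest, the final visit of the final participant. Two conditions apply: procedural success and no recurrence.
- **Section 2.7.1 (Sample Size Estimation):** "the ICDs will be remotely interrogated via telemonitoring for patients with no recurrence until" the same two end points. Only one condition applies: no recurrence.
- **Section 2.3.2 (Endocardial Approach Only):** "If VT remains inducible despite endocardial ablation, patients will continue follow‐up as per protocol".
- **Table 1:** remote monitoring appears in the post-24-month column without restriction.
- **Sections 2.3.2 and 2.3.3 (definition of success):** "Acute procedural success will be defined by both the absence of VT inducibility on programmed ventricular stimulation and complete substrate modification". This is judged at the end of the randomised procedure.
- **Section 2.6.2 (Secondary Outcome):** one component of success is compared between arms as an outcome, namely "the number of patients with non‐inducibility at the end of the procedure".
- **Section 2.6.1 (Primary Outcome):** "Patients without recurrence will be censored on the date of the last ICD interrogation".
- **Section 2.7.2 (Statistical Analysis):** the primary comparison is a log-rank test.

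**The concern.** The log-rank test relies on censoring that is unrelated to prognosis within each arm. Under section 2.7.1, censoring after 24 months is administrative: everyone still free of recurrence is observed to one calendar date. Under section 2.4, a recurrence-free patient with a failed procedure leaves the risk set at about 24 months, while an otherwise similar patient with a successful procedure stays in it. The section 2.6.1 censoring rule carries that difference into the primary analysis.

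Success is known only after randomisation, and it may not mean the same thing in the two arms. In the endocardial arm it is judged on one mapped surface, in the combined arm on two. Section 2.3.3 also accepts that some epicardial targets may not be ablatable, given the phrenic nerve and coronary arteries. If failure predicts recurrence and is distributed differently by arm, the section 2.4 rule removes higher-risk patients unequally from the late part of the curves.

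The late data matter. The article's own risks give slightly fewer than the required events by 24 months, so extended follow-up is part of how the target is reached.

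**Working it through.** **1. Reproducing the planned event number.** Inputs from section 2.7.1: HR 0.43, 90% power, two-sided 5%; 1:1 allocation from section 2.1. Schoenfeld: events = 4(1.960 + 1.282)² / (ln 0.43)² = 59.0. The stated 59 is reproduced. The HR also agrees with the stated risks: ln(0.74)/ln(0.50) = 0.434.

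**2. Events by exactly 24 months.** 75 × 0.50 + 75 × 0.26 = 37.5 + 19.5 = 57. Power with 57 events is about 89%.

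**3. Events with unrestricted follow-up.** Assume exponential times and uniform accrual over A months, so follow-up runs from 24 to 24 + A months. The expected proportion recurrence-free per arm is S(24) × (1 − e^(−λA))/(λA).

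- Endocardial: λ = ln 2/24 = 0.0289. With A = 36, the proportion is 0.50 × 0.622 = 0.311, giving 75 × 0.689 = 51.7 events.
- Combined: λ = −ln(0.74)/24 = 0.01255. With A = 36, the proportion is 0.74 × 0.805 = 0.595, giving 75 × 0.405 = 30.3 events.
- Total: about 82, of which 82 − 57 = 25 (30%) arise after month 24.

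The 36 months is an assumption (60 months' total duration minus 24). Section 2.1 gives a recruitment end of October 2028, which is itself 60 months after the start, so accrual is not fixed by the text. With accrual of 12, 24 and 60 months the totals are 67, 75 and 93.

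**4. Effect of the section 2.4 rule at the design effect.** Simulation of 75 patients per arm, two-year risks held at 50% and 26%, 36-month accrual. Failures are either followed to study end (full) or censored at 24 months (restricted). Failure rates and the hazard multiple after failure are assumptions.

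| Failure, endocardial / combined | Hazard multiple | Events, full → restricted | Power, full → restricted | HR, full → restricted |
|---|---|---|---|---|
| 20% / 20% | 2 | 81 → 76 | 96% → 95% | 0.434 → 0.431 |
| 20% / 20% | 3 | 80 → 75 | 95% → 95% | 0.438 → 0.427 |
| 40% / 20% | 2 | 81 → 73 | 96% → 93% | 0.436 → 0.443 |
| 40% / 20% | 3 | 79 → 72 | 95% → 92% | 0.444 → 0.449 |
| 20% / 40% | 2 | 81 → 73 | 95% → 95% | 0.434 → 0.424 |
| 20% / 40% | 3 | 80 → 73 | 95% → 96% | 0.438 → 0.414 |
| 40% / 10% | 3 | 80 → 74 | 94% → 90% | 0.448 → 0.464 |

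Over the pairs 30/30, 40/20, 50/15 and 20/40 with multiples of 2 and 3, events are 71–74 against 79–81, and power is 88–96% against 94–96%. The lowest power is at 50% versus 15% with a threefold hazard. With a weaker true effect (50% versus 35%), failures of 40% versus 20% and a twofold hazard, power falls from 60% to 52%.

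**5. Effect when there is no treatment difference** (two-year risk 40% in both arms; rejection in favour of the combined approach, nominal 2.5%).

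| Failure, endocardial / combined | Hazard multiple | HR, full → restricted | Rejection, full → restricted |
|---|---|---|---|
| 20% / 20% | 2–3 | 1.00 → 1.00 | 2.3% → 2.1–2.3% |
| 40% / 20% | 2–3 | 1.00–1.01 → 1.03–1.05 | 2.1–2.2% → 1.2–1.5% |
| 20% / 40% | 2–3 | 0.99–1.00 → 0.95–0.97 | 2.3% → 3.1–3.8% |
| 10% / 40% (extreme) | 3 | 0.98 → 0.92 | 3.1% → 5.5% |

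To isolate a difference in the meaning of success, both arms were given identical recurrence times with 30% high-risk patients at a threefold hazard. When failure identifies all of them in one arm and none in the other, the HR moves from 1.00 to 1.06 or 0.94, depending on the arm.

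**The case against.** A reader might infer that the primary log-rank test is informatively censored by design. The document does not support that. Section 2.7.1, which justifies the extended follow-up, contains no success condition, and section 2.3.2 and Table 1 fit it. Section 2.4 is the outlier, and the harm arises only if it is the rule applied. Nor does the article say that its phrase in section 2.4 is the acute procedural success defined in sections 2.3.2 and 2.3.3; that is the natural reading, but an inference.

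The only evidence in the article on success by arm points to no imbalance. Of a meta-analysis, the Discussion reports: "No differences in terms of acute procedural success nor all‐cause mortality were observed". With equal failure rates and the same prognostic meaning, the bias is negligible. This objection stands in part. Those data are observational, no rates are given, and section 2.7.1 concedes that ablation strategies varied widely across the studies behind the treatment-effect estimate. A difference is possible but not shown.

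A reader might also take the 57 events at 24 months as a threat to the event target. That does not follow. More than 59 events are expected under either rule across the assumed range with 36-month accrual, and 57 events would still give about 89% power.

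Finally, if the endocardial arm fails more, the restricted rule works against the superiority claim. This is correct, but which arm will fail more is unknown.

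**Conclusion.** The contradiction is real and should be fixed. The article states two rules for who contributes primary-endpoint time after 24 months, and one of them selects on a post-randomisation result. It does not show that the trial's primary test is biased. Bias requires that section 2.4 is followed, that success predicts recurrence, and that its rate or meaning differs by arm.

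Under the assumptions above, the consequence is modest: about 7–9 of some 80 events lost, 71–74 remaining, and power of 88–96% instead of 94–96%. The one-sided false-positive rate reaches about 4% if the combined arm fails more (20% versus 40%), and the test is conservative if the endocardial arm does. Only the extreme 10% versus 40% case goes beyond that. Failure rates, the hazard after failure and the accrual period are all assumed; the article gives none of them. The required 59 events and the 150 patients are unaffected. This is a should-fix rather than a fatal flaw.

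**What to change.** Remove the procedural-success condition from the section 2.4 sentence, so that every patient in the modified intention-to-treat set without recurrence is followed remotely to the final participant's final visit, as section 2.7.1 already states. Apply this to patients already enrolled. Recruitment began in October 2023, so the earliest patients reach 24 months from about October 2025, which is when the two rules diverge.

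Align section 2.1, which limits each patient's participation to 24 months from ablation, with the remote follow-up beyond that point.

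The cost is small: wording changes in two sections and a note to sites. Remote ICD monitoring is an entry criterion, so no extra visits are needed, and the event number and sample size stay as they are. If the patient information repeats the 24-month limit, it needs checking too.

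Censoring everyone at 24 months would also remove the selection, but it leaves 57 expected events and about 89% power, so it is the weaker choice.

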### Data Collection and Management

2.5

#### Data Collection

2.5.1

The measurement time points for each assessed parameter are shown in Table 1. Descriptive data for the study population will be collected before the ablation procedure. These data will be presented using descriptive statistics.

**Table 1 jce16630-tbl-0001:** EPIC‐VT protocol.

	Inclusion visit		Randomization	D‐1		Radiofrequency Ablation	Before hospital discharge		6‐month follow‐up phone call^a^ (M6 ± 1 month)		12‐Month consultation (M12 ± 1 month)		18‐month follow‐up phone call^a^ (M18 ± 1 month)		24‐Month consultation (M24 ± 1 month)		Data collection post 24 months	
Actions	CP	AR		CP	AR		CP	AR	CP	AR	CP	AR	CP	AR	CP	AR	CP	AR
Information and Consent		X																
Verification of Selection Criteria		X																
Pregnancy Test		X																
Verification of Medical History	X																	
Standard Preoperative Biological Assessment				X														
Echocardiography							X											
Clinical Examination	X			X			X											
ICD Interrogation							X											
Medications Taken	X			X			X			X		X		X		X		
Imaging (Exclusion of Thrombus)				X^b^														
Inquiry About Adverse Events							X			X								
Remote monitoring (VT/VF episodes)										X		X		X		X		X

Abbreviations: CP = clinical practices, AD = added by the Research.

^a^
or during a scheduled consultation;

^b^
From 1 Month to 1 Day Before.

